## Abstract

**Background:**

Medicines management for people with dementia is a global health priority. Cognitive difficulties, such as memory problems, can impact safe and effective medicines management. With appropriate support, people with mild–moderate dementia can self-manage medicines, with and without family. People with dementia can enhance medicines safety by building resilience into their medicines management system through their ability to respond, learn, monitor and anticipate. Medicines self-management interventions have more often focused on adherence as opposed to other experiences, such as knowledge of medicines, though psychosocial interventions have addressed other components of medicines self-management. Co-design approaches draw on the person's experience. A co-designed resilience-enhancing psychosocial intervention for medicines self-management for community-dwelling people living with dementia and with or without family carers (MAGNET) was developed. This protocol describes a study aiming to assess the feasibility and acceptability of the MAGNET intervention.

**Methods:**

Study objectives are to assess the feasibility and acceptability of implementing the MAGNET intervention in preparation for a randomised controlled trial; to develop materials for estimating the effectiveness and cost-effectiveness of the intervention in a randomised controlled trial, and to assess the feasibility and acceptability of collecting data using these materials. This is a non-randomised feasibility study. Seventy-two people living with dementia and their family carers will be recruited to the study and receive the MAGNET intervention. The intervention involves an 8-week community-based medicines self-management programme involving a ‘Managing My Medicines’ guide for people living with dementia and carers, and a medicines self-management professional's guide to support implementation by trained professionals. Methods of evaluation include questionnaires and interviews with people living with dementia, family carers and professionals. Intervention delivery will be observed. Quantitative and qualitative data will be completed at baseline, end month 1, end month 2, and post intervention. The evaluation will be underpinned by the Consolidated Framework for Implementation Research (CFIR).

**Discussion:**

This study will indicate whether the MAGNET intervention is feasible and acceptable. If the study findings support feasibility and acceptability, then we will seek further funding for the development and implementation of a randomised controlled trial.

**Trial registration:**

ISRCTN 15712227.

## Background

Medicines management for people living with dementia is a global health priority. Approximately 50 million people worldwide are living with dementia [1]. Polypharmacy and comorbidities have a higher prevalence in those with dementia compared to those without. The complexity of medicines management for people living with dementia can be impacted by cognitive difficulties, such as memory problems; medication-related factors, such as medication error; social factors, such as family carer support; and communication and health literacy, such as the ability to understand a complex regimen [2]. There is a two-way relationship between health literacy and cognitive ability [3]. Medicines management issues include limited holistic approaches and communication between professionals, and family carers lacking guidance on medication management [4]. A scoping review underscored the significant challenges to medication management information needs faced by people living with dementia and their family carers [5]. The most frequently reported challenge identified in the review was missing, limited, or not useful critical medicine information [6–28]. There was a need for simpler tailored relevant information [18, 29].

A self-management approach has the potential to support safe and effective medicines management for people living with dementia and family carers. Self-management typically involves drawing on one’s own knowledge and skills; goal setting; monitoring behaviour and evaluation [30]. Family carers also need to be considered in self-management interventions as they are frequently involved in dementia care in the home [31]. Benefits of a self-management approach include enhancing quality of life, self-efficacy, knowledge, skills to manage illness and reducing stress [32]. Such improvements have been found for those living with mild–moderate dementia [31, 33]. Moreover, patients can enhance safety by building resilience into their medicines management system [34]. A resilient healthcare (Safety II) approach emphasises how the flexibility and adaptability of healthcare systems result in safer outcomes in the face of fluctuations in normal system operations and disruption. Resilience abilities can include: ability to respond, such as being able to respond to changes; ability to monitor, awareness of what to look out for; ability to learn, awareness of what has happened and being able to learn from this; and ability to anticipate, such as knowing what to expect [35]. Patients and their families have a key role in this process for medicines management [34].

We conducted a systematic review to identify the existing evidence about interventions to support medicines self-management for people living with dementia (or cognitive impairment), and family carers in medicines self-management [36]. Definitions of medicines self-management more often emphasise adherence, whereas patient perspectives are more evident in studies of health literacy [37]. The patient’s experience of medicines self-management can include checking for errors, seeking support, adherence, knowledge, supply management and monitoring effects [34, 38–40]. We further checked our understanding of the definition through discussions with a patient public involvement (PPI) group that was identified and invited through an existing university PPI network. An online meeting was held, followed by a phone meeting, and correspondence via email. Further information about the PPI group’s involvement can be seen in the systematic review paper [36]. We screened articles for medicine self-management components and resilience capabilities. Key findings from the systematic review indicated that people living with dementia or cognitive impairment and their family carers need support with self-management of medicines. Interventions primarily focused on improving adherence through providing reminders via devices and pictures [41], rather than addressing other key person-centred experiences of medicines self-management such as re-ordering, checking supplies and error resolution, seeking support about medicines from healthcare professionals, monitoring effects and side-effects, and having knowledge about medicines. Medicines self-management interventions for people living with dementia and family carers that aim to enhance resilience were limited. However, psychosocial interventions showed some promise in addressing a broader conception of medicines self- management, had stronger theoretical underpinnings in social cognitive and self-efficacy theories, and enhanced a greater number of resilience outcomes [42, 43]. All interventions lacked patient public involvement (PPI) in their development, a co-design approach, and none were UK-based. Not involving end users in intervention development through co-design will limit the effectiveness in addressing real needs and patient priorities, that go beyond adherence [36].

Thus, there is a need for a co-designed theoretically informed psychosocial intervention that enhances resilience, and supports not only adherence to medicine regimes, but more aspects of self-managing medicines when living with dementia, including re-ordering, checking supplies and error resolution, seeking support from health care professionals with medicines, monitoring effects and side effects, and having knowledge about medicines.

In the first two phases of the MAGNET programme, using the theory of resilience in healthcare, we explored how people with mild-moderate dementia (with and without their family) self-managed their medicines. Using an Experience-Based Co-Design (EBCD) approach, we co-designed an intervention with people living with dementia, family carers, health, social care, and voluntary sector professionals who regularly support safe medicines self-management. EBCD is a participatory method, where patients, the public, and professionals involved in a service are brought together to co-design services [44]. Whilst this method is usually conducted in single organisations for service improvement purposes, EBCD has been adapted in several ways [45], including implementation across multiple sites and for research purposes [46]. The first and second phases of the MAGNET programme will be published in separate papers. In this third phase of the project, we will assess the feasibility and acceptability of the MAGNET intervention.

## Methods

Our key aim is to assess the feasibility and acceptability of the MAGNET intervention.

Our key objectives are to:i)Assess the feasibility and acceptability of implementing the MAGNET intervention in preparation for a randomised controlled trial.ii)Develop materials for estimating the effectiveness and cost-effectiveness of the intervention in a randomised controlled trial.iii)Assess the feasibility and acceptability of collecting data using these materials.

If the results support feasibility and acceptability:We will use the findings to inform the development and implementation of a future randomised controlled trial, for which we will seek onward funding,Have a proposal for a randomised controlled trial if appropriate.

### Design

This study will use a non-randomised feasibility design and will follow the SPIRIT 2013 guidelines [47] and reporting template (Additional file 1). A non-randomised design is selected because we are concerned with the feasibility and acceptability of the MAGNET intervention, not measuring effectiveness. The non-randomised design will provide us with data about how the intervention could work within real-world settings. Moreover, time and resources are limited within a planned two-year multiphase programme involving exploring how people with mild-moderate dementia (with and without family carers) self-manage medicines, co-designing an intervention, and conducting a feasibility study. We recognise the limitations that a non-randomised study can introduce through for example selection bias and providing misleading results [48]. Hence, we aim to conduct a randomised controlled trial when measuring effectiveness should the intervention be proved feasible and acceptable following this feasibility study. A schedule for study procedures is provided in Table 1.

**Table 1 Tab1:** Study procedures

Procedures	Visits					
	Screening	Baseline	Months			Post intervention
			Start 1	End 1	End 2	
Informed consent people living with dementia and family carers	X					
Informed consent of professionals	X					
Questionnaires with people with dementia and family carers		X		X	X	X
Interviews with people with dementia and family carers						X
Interviews with professionals						X
Observation of intervention delivery			X			
Intervention delivery (including staff training, guide delivery)		X	X			
Phone calls between professionals and people with dementia and family carers				X		

### Intervention

The MAGNET intervention is delivered over 8 weeks. Materials include: the MAGNET guide for professionals to implement the intervention, the MAGNET guide for people living with dementia and their family, a short video summary of the intervention a reminder postcard, and associated training for professionals. The training for professionals comprises two sessions of 45 min each, which can be delivered online or in person. Professionals will deliver the intervention, ‘Managing My Medicines’ Guide, to the person (and family carer if relevant) and facilitate the identification of key goals and actions related to medicines self-management. After 4 weeks, the professional will contact the person (and family carer if relevant) to provide further support as required. Due to the diverse population and services delivering the intervention, how long the professional will spend at each visit will vary. Some professionals will be delivering the intervention as an add-on to the usual care visit. We anticipate the first visit lasting 45 min, and the follow-up visit lasting 30 min.

### Recruitment

Figure 1 below shows how sites and participants will be identified and recruited to the study.

**Fig. 1 Fig1:**
[figure not shown]
Recruitment process

The National Institute for Health and Care Research, Research Delivery Network (RDN) will send out expressions of interest to English NHS Trusts, to identify eligible sites. The research team will also identify relevant organisations through internet searches and networking, followed by in-person or online meetings to further engage with interested sites. Eligible sites will be those supporting people who are living with dementia, including mental health trusts, community health trusts, general medical practices (GPs), memory clinics, primary networks, local councils, community pharmacies, social enterprises, and research platforms.

The study team will liaise with recruitment sites for ideas and suggestions about how a diverse sample can be achieved. The participation of sites such as GPs, community health trusts, memory clinics, social enterprises will enable invitations for participation to reach a wider and more diverse population.

### Participants

We plan to recruit 72 participants who will be community-dwelling people living with dementia and family carers will also be invited to participate. Professionals will be recruited from the health, social care or voluntary sector. We will decide whether participants will be eligible to engage in the study on a rolling basis in a future randomised controlled trial when we consider the results of the feasibility study.

### Inclusion criteria

People living with dementia will be eligible to take part if they are.Living with mild-moderate dementia (as indicated by a Mini-Mental State Examination [49] score between 24 and 10 or a clinical diagnosis of mild-moderate dementia).Using two or more medicines.Living at home.Living alone or living with family carers.

Family carers will be:Relatives, friends or neighbours identified as involved in supporting the person with their medicines.Caring for the person with mild-moderate dementia (as indicated by a Mini-Mental State Examination [49] score between 24 and 10, or a clinical diagnosis of mild-moderate dementia), using two or more medicines, and living at home.May be living within or outside the household of the person with dementia.

Professionals will be.Health, social care or voluntary sector professionals who support people with dementia and family carers or researchers with relevant health, voluntary or social care background.

### Exclusion criteria

People with dementia will be excluded if they are any of the following:Using fewer than two medicines.Living in care homes.Live with moderate to advanced dementia.Lack capacity to consent.On the End-of-Life Pathway.Unable to communicate verbally.

Family carers will be excluded if they are either of the following:Not a relative, friend or neighbour identified as involved in care for the person in this study.The person they are caring for has advanced dementia, using fewer than two medicines, and/or not living at home.

Professionals will be excluded if they are any of the following:Have no involvement with patients with mild-moderate dementia living at home or are not researchers with a relevant health, voluntary or social care background.Have no involvement with patients with mild–moderate dementia, on two or more medicines or are not a researcher with a relevant health, voluntary or social care background.

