### Sample size

We will recruit 72 people living with mild-moderate dementia and family. We predict that, with dropout, 60 recruited participants would yield a sufficient response rate to meet the study objectives. Health, social and voluntary sector professionals will be recruited across the three healthcare areas. The sample size of professionals is dependent on how many professionals are required at each organisation to deliver the intervention. We will liaise with sites directly to discuss capacity and capability at each organisation. We anticipate approximately 27 professionals will be recruited.

Given this is a non-randomised feasibility study, a formal sample size calculation is not needed [50]; however, statisticians at a clinical trials unit were consulted for advice. The sample size is based on the need to estimate the recruitment rate, and our knowledge of numbers available and recruitment method [51]. We aim to understand if we can consistently recruit 72 over a period of 6 weeks, four a week for 6 weeks in three sites. We will analyse drop-out rates for the 72 as the intervention is delivered. We predict that, with drop-out, 60 recruited patients would yield a sufficient response rate to meet the study objectives. The decision on 60 recruited participants (30 people with dementia/family carer dyads) was based on the general rule that at least 30 participants or greater are needed to estimate parameters [52, 53]. Should we apply for a randomised control trial, we will use data from the feasibility study to inform the parameters used for the estimation of the sample size.

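### People with moderate dementia meet both the inclusion and an exclusion criterion, which leaves eligibility counts and site recruitment rates ambiguous

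*Protocol article*

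**What the plan says.** **Person with dementia, inclusion (Inclusion criteria).** "Living with mild-moderate dementia (as indicated by a Mini-Mental State Examination [49] score between 24 and 10 or a clinical diagnosis of mild-moderate dementia". The two routes are alternatives, so a clinical diagnosis is enough without a score.

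**Person with dementia, exclusion (Exclusion criteria).** Meeting any one listed item excludes. One item is "Live with moderate to advanced dementia". It carries no score and no definition.

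**Family carers.** The inclusion list repeats the same MMSE range and diagnosis for the person cared for. The exclusion list uses a different term: "The person they are caring for has advanced dementia, using fewer than two medicines, and/or not living at home".

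**Professionals.** Again any one item excludes, and the first reads "Have no involvement with patients with mild-moderate dementia living at home or are not researchers with a relevant health, voluntary or social care background". The second bullet, on patients using two or more medicines, is built the same way.

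**Target population and rate (Sample size).** "We will recruit 72 people living with mild-moderate dementia and family", and "We aim to understand if we can consistently recruit 72 over a period of 6 weeks, four a week for 6 weeks in three sites". The Background and Ethics sections also describe a mild-to-moderate population.

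**Outputs that depend on eligibility.** Table 2 item 1 counts those screened, eligible and consenting. Item 7 carries drop-out and eligibility forward to the sample size of a definitive trial. Table 3 sets the recruitment progression bands per site per week: green 3–4, amber 2, red below 2.

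**The concern.** The two severity rules for the person with dementia overlap at moderate dementia. If one site follows the inclusion line and another the exclusion line, the same candidate is eligible at the first and ineligible at the second. The number eligible, the ratio of eligible to screened, and recruits per week would then partly reflect which line a site followed, and not only how feasible recruitment is.

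This touches the study's main purpose. The Sample size section says that the number was chosen to estimate the recruitment rate, and that rate is one of the four progression criteria. If every site followed the exclusion literally, the sample would be mild only. Its recruitment, delivery and completion figures would then describe a narrower group than the mild-moderate population for which the future trial is being prepared.

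**Working it through.** **1. Set the severity rules side by side.**

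| List | Mild | Moderate | Advanced |
|---|---|---|---|
| Person, inclusion | in | in | not included |
| Person, exclusion | not excluded | excluded | excluded |
| Carer, inclusion (severity of person cared for) | in | in | not included |
| Carer, exclusion (severity of person cared for) | not excluded | not excluded | excluded |

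The first two rows conflict in the moderate column. The conflict needs no MMSE cut: a person clinically diagnosed with moderate dementia falls under both rules whatever the score. The two carer rows agree with each other. They differ from the person-level exclusion, so under a literal reading a carer can be eligible when the person cared for is not.

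**2. Look for a sentence that resolves it.** There is none: no order of precedence, no boundary between mild and moderate, and no definition of the excluded band. Capacity to consent and verbal communication are separate exclusions, so the severity line is not needed as a stand-in for either.

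**3. Reproduce the plan's own figure.** Four per week × 6 weeks × 3 sites = 72. Table 3 gives the same total: 12 per week × 6 weeks = 72.

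**4. Illustrate how the rule could reach the progression decision.** The article gives no share of candidates with moderate dementia, so the share s is an assumption and is shown over a range. Suppose that a site would recruit 4 per week under the inclusion line, and that a share s of those recruits has moderate dementia. Under the literal exclusion the site recruits 4(1 − s) per week. If all three sites did so, the total would be 4(1 − s) × 18 site-weeks.

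| Assumed s | Per site per week | Total | Table 3 band |
|---|---|---|---|
| 10% | 3.6 | 64.8 | green |
| 25% | 3.0 | 54.0 | lower edge of green |
| 30% | 2.8 | 50.4 | below green |
| 50% | 2.0 | 36.0 | amber |
| 60% | 1.6 | 28.8 | red |

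The rate drops below 3 when 4(1 − s) < 3, that is s > 25%. It drops below 2 when s > 50%. Two otherwise identical sites that follow different lines differ by 4s per week, for example 4 × 0.25 = 1 per week at s = 25%. These are conditional results, not estimates.

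**5. Professional bullets.** As written, the rule excludes a person who has no involvement with such patients *or* is not a researcher with a relevant background. A nurse or pharmacist who sees these patients but is not a researcher meets the second half and is excluded. The inclusion list admits exactly such professionals. With *and* in place of *or*, only someone who is neither involved nor a relevant researcher is excluded, which agrees with the inclusion list.

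**The case against.** The best defence is that the intended population is clear from context. The only operational definition of severity is the MMSE range or diagnosis, and it appears in both the person and carer inclusion lists. The Background, Sample size and Ethics sections say mild-moderate, and the carer exclusion says advanced only. One discordant line looks like a drafting slip, and a site might read it as the band beyond mild-moderate. This is plausible, but the article does not say so, the line has no cut-off, and sites as varied as memory clinics, councils and pharmacies have no common reading to fall back on.

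A reader might infer that sites **will** diverge and that the rates **will not be interpretable**. The article does not support that. Sites may all read the line the same way. The Feasibility study outcomes section also commits to recording numbers screened, eligible and consented, reasons for non-recruitment, and the steps sites take. Exclusions for severity could therefore be visible afterwards. This limits the damage but does not repair the rule.

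A reader might also gauge the size by the fraction of the MMSE range that counts as moderate. That needs a cut the article does not give. It also counts score points rather than people, although candidates need not be spread evenly over the range and some enter by diagnosis without a score.

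Nor is the carer exclusion an independent third boundary. It agrees with the carer inclusion list, and its mismatch is the same person-level conflict seen from another list. The professional slip is real but secondary, since the inclusion list makes the intent clear.

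**Conclusion.** The contradiction stands on the printed text: moderate dementia is both included and excluded, and nothing settles which rule applies. The consequence is ambiguity in the eligibility counts and in the per-site recruitment rate, with a mild-only sample if the exclusion is taken literally. Its size cannot be stated. The illustration shows only that the progression band could change if more than a quarter of otherwise recruitable people have moderate dementia. It assumes a starting rate of 4 per site per week and loss in proportion to that share. Because the analysis is descriptive and there is no comparison group, no effect estimate is at risk. The point concerns who was counted and which population the feasibility figures describe.

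**What to change.** 1. The investigators should reconcile the inclusion and exclusion criteria to one defined severity boundary, used identically in the person inclusion, person exclusion and carer lists. Where the boundary lies is for them to decide.
2. Reissue the site screening form with that boundary, covering both the score route and the diagnosis route.
3. If recruitment has begun (the article does not say), record which rule each site applied and report screening and recruitment by severity, so that the Table 2 counts and the Table 3 rate can be read on a common basis.
4. In both professional exclusion bullets, change *or are not* to *and are not*.

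The cost is small: a wording amendment through the approval route described under Ethics and a revised form. If sites are already open, there is also a short retrospective check of their screening records.
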